**Introduction**

Aging is accompanied by an increase in the prevalence rate of chronic diseases and functional disabilities(1). However, compared to past generations, today's older adults have better functional ability(2). The majority of older people prefer to age in place, remaining autonomous, active and independent in their own home and surrounded by family and friends (3). On the other hand, some older people do not have a large social network, and loneliness is one of the most challenging issues that makes living at home hard for older people(4). The prevalence of loneliness increases among older adults; Jylhä noted that age may not conclusively be a causal factor for feeling lonely, however increasing disability and decreasing social integration with increasing age may be a dominant factor (5).

Loneliness is a negative and unpleasant feeling of stress, which may be experienced through a lack of social contacts(6). Although loneliness is synonymous with social isolation, they are conceptually different(7). Social isolation is an objective condition of having minimal contact with other people, while loneliness refers to a subjective feeling which is perceived by only an the individual alone(8). For instance, individuals may be participating in social gatherings, but they may still suffer from feeling of loneliness. An individual may be socially active but feels alone, and conversely, another individual may not feel alone despite being isolated(9). In other words, loneliness is not related to frequency of contacts with people, but instead to the quality of relationships and meaningful engagement with others (10).

Based on previous studies, approximately one third of older people experience loneliness in later life (11-13). The rate of loneliness increases with age, particularly in individuals aged 80 and older(14). Some factors, including death of a spouse, health deterioration, decreased social contacts, hospitalization, and enhanced functional disability may increase risk of loneliness(15, 16), which in itself may be a risk factor for functional disability and reduced social contacts (17), and depression (18) among older adults. Older adults consequently may also experience difficulties to perform activities of daily living independently (19), but would be relying on informal care services in their home(20). Therefore, the older adults' home seems to be an ideal location for interventions and short-term and long-term care services provided by health practitioners, health care providers, specialists, and informal caregivers (21). Although there are centers that provide home health care services for older adults, these centers are challenged by financial difficulties and inappropriate infrastructure(22, 23).

To provide older adults with informal home care services, comprehensive strategies could be applied to provide a platform for participation of all stakeholders. The use of appropriate technology such as online social networks can support the implementation of these strategies(24). Maintaining meaningful social relationships is considered an important elements of healthy aging(25). The geographical distance from relatives and/or functional disabilities may prevent older adults from having social contact, which may result in increased loneliness (26). Therefore, the use of social media may help older individuals in communicating with each other regardless of geographical location and time(26, 27). That is "*Social media are Internet-based channels that allow users to opportunistically interact and selectively self-present, either in real-time or asynchronously, with both broad and narrow audiences who derive value from user-generated content and the perception of interaction with others*(28)."

Social media may provide opportunities for creating social connections, giving and receiving social support, and enhancing a sense of control over life(29). Receiving emotional support through an online social network could lead to improving functional outcomes among older people(29). Communication and having relationships with other older adults and friends through online social networks might increase social cohesion and promote social networks. In the context of such social networks, older people can provide each other with emotional, instrumental, communicative and informational support (30). Stevens et al. found that telephone calls and home visits by peer volunteers, who had similar characteristics, could improve physical activity in older adults(31). In fact, communication with peer group members can be an effective way to reduce loneliness, disappointment, and social isolation among lonely older adults, and consequently decreasing psychological distress and mortality among older people(21). Volunteer peers can also play a crucial role in providing peer support and community-based social support. Older adults are likewise very committed to provide peer support as volunteers as they spend more time on community-based services, compared to other age groups (22).

According to the helper therapy principal (HTP), in the context of peer support, individuals receive mutual benefit during contact with peers(32). The HTP describes that when an older adult provides a specific service for other older adults, the person providing supports also receives benefits, including information exchange, emotional benefit, and increased level of social contacts(33). In such an environment, older adults are able to share their opinions and perspectives peaceful environment without worry or fear(34). This approach has reciprocal advantages including improved self-efficacy by helping others and increased self-knowledge and skills because of shared common experiences(32, 35).

In Iran, as a developing country, studies on the provision of the informal supportive home care for older adults are in their infancy. Current evidence on home care services for older adults are limited to some qualitative studies on exploring the barriers of home care programs (23), the role of family support in home care (36), and the necessity of providing health home care services(22). So, there is a need to investigate the feasibility of interventions that focus on informal home care programs provision involving volunteer peer supports as a cost-effective and mutual beneficial program for those involved.

**Conceptual framework**

In the present study, the conceptual framework of peer support, originating from the social support theory, will be used to develop a home care program for older adults(37). This framework is based on an online social network, and consists of four components including emotional, informational, instrumental, and affiliational support (37, 38). Emotional support (lonely older adults provide empathy, care, counsel for their peers, and help each other) may build self-confidence and self-esteem (38); Informational support is the process of knowledge transfer such as health information, educational assistance, learning new skills (vocational or art courses), and learning about their right by peers(38); Instrumental support comprises the support of peers in performing instrumental activities of daily living (e.g. shopping, cooking, using transportation)(39).; and Affiliational support includes the support of peers in making social relationship between a group of older adults with similar characteristics (living alone), reinforcing the sense of belonging(38).

In fact, peer support could have mutual benefits for both older adults and peer helpers. Our aim is to investigate, if solitary older adults receive the mentioned supports from their older adult peers and how it affects their social network, social support, and self-care ability. Fig 1. shows the conceptual framework designed based on social support model.

**
[figure not shown]
**

The conceptual framework designed based on social support model

**The main objective**

Design, Implementation and evaluation of a Home Care Support Intervention Program for lonely older adults in Gorgan.

**The feasibility of conducting the study**

The implementation process of the current study and the intention of generalizing the results to a larger population will be accompanied by several challenges. The research team will try to tackle these challenges through using feasibility components. Some possible challenges are also pointed out: 1- the reluctance of older adults to participate in the study due to lack of interest in changing their past lifestyle, lack of older adults' knowledge about the benefits of participating in such programs; 2- the possible loss of sample size; 3- lack of researcher's knowledge about older adults' compliances to the intervention program; 4- Safety and ethical issues related to the presence of older adults in each other's house; 5- older adults who will participate in the intervention program may have a higher motivation than those who will refuse to participate; 6- if women older adults participate in this study, the possibility of generalizing the results to a larger population will be questioned; 7- because of cultural issues, provision informal supportive services by lonely older men who don't have family ties may be challenging for lonely older women. Therefore, in order to evaluate the feasibility of home care informal support care services, five criteria related to feasibility study will be evaluated (Objectives and Guiding Questions for a Feasibility Study-supportive file 3).

Objective 1: Evaluation of Recruitment Capability and Resulting Sample Characteristics.

Objective 2: Evaluation and Refinement of Data Collection Procedures and Outcome Measures

Objective 3: Evaluation of Acceptability and Suitability of Intervention and Study Procedures.

Objective 4: Evaluation of Resources and Ability to Manage and Implement the Study and Intervention

Objective 5: Preliminary Evaluation of Participant Responses to Intervention

**The definition of specific words**

**1- Concurrent nested method**

**Theoretical definition**: In this model, both qualitative and quantitative data are being collected at the same time. Qualitative data are embedded in the quantitative design(40).

**Practical definition:** in this study quantitative questionnaires and semi-structured interview will be conducted simultaneously to evaluate the intervention program.

2- **Home care**

**Theoretical definition**: Home care services are suitable for older adults who would like to live in their homes until the end of their lives. These services are provided in two ways: personal care and informal help services(41).

**Practical definition**: in this study, lonely older adults will perform some informal support (instrumental, informational, affilitional and emotional) for each other at home and in community.

**3- aging**

**Theoretical definition**: Older adults who are at the age of 60 and over and they experience changes in different aspects, i.e. physical, psychological and social (42).

**Practical definition**: in this study we will consider older adults at the age of 60 and over

**4- peer support**

**Theoretical definition**: peer supporters are people who have the same characteristic as person who is in need of help. Peer supporters usually provide each other emotional and social support in the community(43).

**Practical definition**: In this study, lonely older adults will provide each other instrumental, informational, affilitional and emotional support.

**5- online social network**

**Theoretical definition**: An online service or site to facilitate social interaction to help individuals find others of a common interest, establish a forum for discussion, and exchange information(44).

**Practical definition**: in this study lonely older adult will be registered in online social network (HAMDAM).

**The ethical considerations**

1- This study is approved by the Research Ethics Committee in Tabriz University of Medical Sciences (IR.TBZMED.REC.1399.488)

2- Verbal and written informed consent from all participants will be obtained.

3- All participants will be informed about using a voice recorder and taking notes from the interviews

4- The time and the place of the assessment (completing questionnaires and interviews) will be chosen by participants

5- The identities of all participants will remain confidential

6- All publications resulting from this thesis should be published under the name of Tabriz University of Medical Sciences.

**Eligibility**

**Inclusion criteria**

Inclusion criteria for both giver and receiver peers are:

1. Aged 60 years and older living in the same from local neighborhoods
2. Able and willing to provide written informed consent
3. Without any cognitive disability based on Abbreviated Mental Test (AMT_10)
4. Not receiving any personal or practical assistance from others
5. Older adults who live alone at home

**Exclusion criteria**

Exclusion criteria includes:

1. Being reluctant to continue study procedures.
2. People with visual and hearing impairments will be referred to related support centers, in the case of not being supported by the Iranian welfare organization.
3. Participating in another healthcare intervention during the previous 12 months

**Method/design:**

We will use a mixed-methods study with concurrent nested design (quantitative and qualitative research methods), HoSIP will be conducted to provide solitary older adults (intervention group) with a 12-week home care service by peer supporters. Quantitative data will be obtained from a cross-sectional study and a pretest-posttest control group intervention study (the pretest will be conducted at the baseline, and the posttest will be performed immediately, three and six months after the intervention period). Qualitative data aiming to identify the feeling of loneliness, quality of life, and general health among participants, as well as strengths and weaknesses of the intervention program, will be collected immediately after the intervention. All participants will complete a consent form before entry into the study. This study will be conducted in three phases including two quantitative stages and one quantitative (qualitative) phase

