**Stage 2:**

**Type of the study:** A qualitative study with content analysis approach will be conducted

**Participants:** The purposive sampling will be used to identify lonely older adults having the lowest and the highest scores at the first post-intervention assessment (at the end of 12 weeks) in outcome variables such as feeling of loneliness.

**Research question:** Based on the participants' experiences, what are the strengths and weaknesses of establishing a social network (HAMDAM) to provide an Informal Home Care Support?

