**Data collection**

The interviews will be conducted at the day care center. The time of each interview is estimated to be 40-60 minutes and it will be planned by mutual agreement based on participants' convenience. The participants will be asked to tell about their experiences associated with the intervention program. The semi-structured guide to the interview questions will be asked after the intervention (12 weeks) are as follows:

1- Based on your experiences with the program, how do you assess the services provision in this intervention program?

2- What problems do you identify in this intervention program?

3- What is the strength point of this intervention program?

4- After participation in the program, have you changed your lifestyle?

5- After participation in the program, do you feel any changes in loneliness? How?

As interviews proceed, some probing questions such as "Please, could you elaborate this a little more ", "why?" and "how”, will be asked for exploring the depth of participants' experience. All interviews will be recorded using a digital recorder and participants' gestures and facial expressions will be noted during interview

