**The Integration of the quantitative and qualitative data**

To achieve a more comprehensive standpoint about the process of the study, an embedded concurrent design will be conducted. Therefore, quantitative data from the intervention program will be merged with qualitative data from semi-structured interviews. This process will provide us with a total scheme on how much the informal home care service package in the format of combination of face-to-face meetings and online sessions take effect on promoting the primary and secondary outcomes**.** Fig 2 shows the whole procedure of the study.

**
[figure not shown]
**

Fig 2. The whole procedure of the study.

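### Quality of life and general health are stated aims of the interviews, but no question in the interview guide asks about either

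*Protocol*

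**What the plan says.** Four parts of the protocol bear on this point.

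- **Method/design** sets the aim: "Qualitative data aiming to identify the feeling of loneliness, quality of life, and general health among participants". The same sentence goes on "as well as strengths and weaknesses of the intervention program, will be collected immediately after the intervention". That makes four aims: three constructs concerning the participants, and one concerning the program.
- **Phase 3, Stage 2** states the research question for the qualitative study: "what are the strengths and weaknesses of establishing a social network (HAMDAM) to provide an Informal Home Care Support". It names none of the three participant constructs.
- **Data collection** (under Stage 2) sets out the semi-structured guide. Question 1 is "how do you assess the services provision in this intervention program", question 2 is "What problems do you identify in this intervention program" and question 3 is "What is the strength point of this intervention program". Question 4 asks about lifestyle change. Question 5 is "After participation in the program, do you feel any changes in loneliness? How". General probes follow, asking the participant to elaborate or to say why and how.
- **The Integration of the quantitative and qualitative data** states that "quantitative data from the intervention program will be merged with qualitative data from semi-structured interviews", so as to give an overall picture of the program's effect on the primary and secondary outcomes.

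**The concern.** The protocol fixes both the purpose of the interviews and the instrument, and the two do not agree. Two of the constructs that the interviews are meant to illuminate have no question.

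What is at stake is the nested design. Its value lies in setting participants' accounts beside their scores. If an interviewee says nothing about health or quality of life, the transcript alone cannot show whether nothing changed or whether the topic was never raised. Stage 2 also selects interviewees with the lowest and highest scores on outcome variables, with loneliness given as one example. If CASP-19 or GHQ-12 scores are used in that selection, a participant could be chosen for an extreme score on a construct that the interviewer then never mentions.

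**Working it through.** There is no figure in the plan to reproduce, so the check sets the sections side by side.

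| Aim in Method/design | In the Stage 2 research question? | Direct question in the guide | Matching questionnaire |
|---|---|---|---|
| Loneliness | No | Question 5 | UCLA-20 |
| Quality of life | No | None | CASP-19 |
| General health | No | None | GHQ-12 |
| Program strengths and weaknesses | Yes | Questions 1, 2 and 3 | None |

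**Counting the questions.** Three concern the program, one concerns loneliness and one concerns lifestyle: 3 + 1 + 1 = 5.

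**Counting the aims.** Two of four have a direct question. Restricted to the three participant constructs, the count is one of three.

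**Could question 4 stand in for the missing ones?** It asks whether the participant has changed how he or she lives, which is about behavior. The Questionnaires section describes GHQ-12 as scoring mental distress, and CASP-19 as covering control, autonomy, pleasure and self-realization. A lifestyle answer may touch on these but does not ask for them.

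**Could the probes?** The listed ones deepen what a participant has already said; none opens a new topic. They are given as examples, so an interviewer is free to add others, but nothing tells the interviewer to.

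**Does the guide simply follow the narrower research question?** Only in part. Questions 1 to 3 fit it. Question 5 goes beyond it and serves the wider aim in Method/design. The guide therefore takes up one of the three participant constructs and leaves two.

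**What follows for the integration.** That section does not list its outcomes. I take CASP-19 and GHQ-12 to be among them, because Phase 3, Stage 1 has both completed in both groups at all three post-tests. For these two scales the guide does not ensure any interview material to merge.

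**The case against.** The strongest reply is that the interview is open. Participants are asked to recount their experience of the program, the probes are not a closed list, and content analysis works from whole transcripts. Under Qualitative data analysis, each interview is analyzed before the next begins, so a missing topic can be noticed and raised with later interviewees. Letting themes emerge is also a legitimate choice. All of this stands, and it limits the point: the two constructs are not systematically elicited, but they are not shut out.

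A second reply is that Method/design is an overview and the Stage 2 research question is the working plan, so one sentence is merely too broad. That is a fair reading, and it supports narrowing the aim as an acceptable remedy. It does not remove the mismatch, because the integration section still promises results on the outcomes generally.

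A reader might infer several stronger things that the document does not support:

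- **That the guide asks only about loneliness.** Four of its five questions concern something else, and the strengths-and-weaknesses aim is well covered.
- **That quality of life and general health cannot be derived or merged at all.** Relevant material may emerge, for the reasons above.
- **That five of the six questionnaires lack a needed interview question.** No section requires one question per scale, and Method/design does not assign social network, social support or self-care to the interviews.
- **That the gap is beyond repair once interviewing starts.** Interview-by-interview analysis leaves room to correct it for later participants, though no second interview is described for those already seen.

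**Conclusion.** The point holds as an inconsistency between the stated aim, the research question and the guide. Two of the four aims of the qualitative data have no direct question, so interview material to set beside the CASP-19 and GHQ-12 results depends on what participants volunteer or interviewers improvise.

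The consequence is confined to the qualitative aim and the integration. A reader might infer that the evaluation of quality of life and general health is itself compromised. It is not: both are measured by questionnaire in both groups, and no group comparison or sample size depends on the interview guide.

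The conclusion assumes that the guide is used as printed, and that the integration is meant to reach these two scales. It should be settled before interviewing begins: it is more than a missing detail, since the protocol sets aims that its own instrument does not pursue.

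**What to change.** **Preferred.** In Data collection, place two open questions beside question 5, worded neutrally so that improvement, worsening and no change are equally easy to report:

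- *Since taking part, has your quality of life become better, become worse or stayed the same? How?*
- *Since taking part, has your general health or mood become better, become worse or stayed the same? How?*

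Widen the Stage 2 research question so that it covers participants' experience of loneliness, quality of life and general health as well as the strengths and weaknesses of the network. The cost is a few minutes in an interview planned at 40 to 60 minutes, with no added visits or staff.

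**Alternative.** Leave the guide as it is, remove quality of life and general health from the aim in Method/design, and limit the integration section to loneliness and program experience. This costs only a text edit, but gives up interview evidence on two constructs that the protocol set out to explore.

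Questions on contacts, support or self-care are not needed to resolve this point.
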